## Methods

### Study design

This study is a Type 2 hybrid effectiveness-implementation randomised controlled trial (RCT), with assessments at baseline, 3, and 12 months. The unit of randomisation and unit of analysis is at the OSHC service level. All participants will provide informed consent to participate. Ethical approval for the study was obtained from the Human Research Ethics Committee of the University of South Australia (protocol number: 204366) and the trial is registered with the Australian and New Zealand Clinical Trial Registry (registration number: ACTRN12622000393752). The conduct and reporting of the trial will adhere to the Consolidated Standards of Reporting Trials (CONSORT) guidelines and the intervention will be described according to the Template for Intervention Description and Replication (TIDieR) checklist.^16^ A rolling recruitment is expected to take place from August 2022 to December 2023, with final follow-up assessments expected to be completed by December 2024.

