#### Effectiveness outcomes

##### Proportion of OSHC care sessions that children spend in moderate-to-vigorous physical activity and recreational screen time

Physical activity and screen time opportunities during a before-school and an after-school care session will be collected at each time point using the System for Observing Play and Leisure Activity in Youth (SOPLAY) direct observation method.^24^ The SOPLAY method involves two trained research personnel conducting continuous visual scans of children’s play zones for an entire care session. For each scan, the time, type of children’s activity, and the number of boys and girls engaged in sedentary behaviour (sitting or standing), light, or vigorous physical activity is recorded.^24,25^ This method has demonstrated acceptable reliability (IOA = 80%) and validity (*r* = 0.75).^26^ against accelerometer-measured physical activity. Interrater reliability will be captured through up to six reliability scans per hour during visits, where both researchers will scan the same zone at the same time. Reliability scans will be compared using Cohen’s kappa (acceptable value ≥ 0.6) and percentage agreement (acceptable value ≥ 80%) for categorical variables, and intraclass correlation coefficients (acceptable value ≥ 0.8) for continuous variables. For each reliability scan timestamp, the final data will be an average of both observers’ data.

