##### Proportion of OSHC care sessions OSHC staff demonstrate physical activity enabling behaviour

Staff behaviour will be collected at each time point using the System for Observing Staff Promotion of Activity and Nutrition (SOSPAN) direct observation tool.^27^ This tool is specifically designed to be used as an adjunct to SOPLAY. After each SOPLAY visual scan, a second scan is performed documenting the presence and behaviour of staff in relation to physical activity (categorised as either engaged, instructing, promoting [enabling behaviours] discouraging, withholding, punishing [disabling behaviours] or off-task). The SOSPAN has demonstrated strong to excellent validity and inter-observer agreement (75–100% agreement).^27^ Interrater reliability will be captured and analysed as per outcome (1).

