### Sample size and statistical analysis

Based on the intervention increasing the proportion of services meeting the OSHC sector physical activity and screen time guidelines by 20% (from 41% expected in the control group to 61% expected in the intervention group), with 80% power, alpha of 0.05, and 3 repeated measures, we will need 75 OSHC services per study arm. To account for drop-out (which our previous experience of research with OSHC services suggests is rare), we will endeavour to recruit 81 metropolitan services in each study arm (total target sample 162 services). An additional fifteen regional services will be recruited in each study arm (total 30), based on the number of eligible services and anticipated response rate.

Analyses will be performed following the intention to treat principles, with the OSHC service as the unit of analysis. Mixed-effects multivariable logistic regression will be used to determine group-by-time changes in the proportion of intervention and control services meeting the OSHC sector physical activity and screen time guidelines. Group-level changes in children’s physical activity and screen time behaviours, and staff behaviour for enabling physical activity will be assessed using mixed-effects Poisson regression. The models will be adjusted by the stratification factors: state and socioeconomic status tertile. If assumptions warrant it, multiple imputation will be used to replace missing data.

Process outcomes will be analysed using descriptive statistics (e.g., % of services taking up the program, % of intervention services agreeing the program is appropriate). Qualitative interview data will be transcribed and analysed using Thematic Inductive analyses.^31^

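### Poisson regression is named for secondary outcomes that are bounded proportions, so its model-based standard errors do not fit the data and can be wrong in either direction

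*Protocol article*

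**What the plan says.** The Outcomes section of the Protocol article defines the child outcome as "Proportion of OSHC care sessions that children spend in moderate-to-vigorous physical activity and recreational screen time" and the staff outcome as "Proportion of OSHC care sessions OSHC staff demonstrate physical activity enabling behaviour". The data behind the child outcome are scan counts: at each scan "the number of boys and girls engaged in sedentary behaviour (sitting or standing), light, or vigorous physical activity is recorded". The denominator, children scanned, is therefore collected. At the timestamps used for reliability scans, "the final data will be an average of both observers" is the rule for the analysed value.

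The section on sample size and statistical analysis then states that "staff behaviour for enabling physical activity will be assessed using mixed-effects Poisson regression", and the same sentence covers the children's behaviours. Analysis is "with the OSHC service as the unit of analysis", adjusted for state and socioeconomic tertile. The trial runs "with assessments at baseline, 3, and 12 months". One before-school and one after-school session are observed at each time point (Procedure).

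The article does not say whether the Poisson response is a count or a proportion. It also gives no offset, no random effect beyond what mixed-effects implies, and no type of standard error. The Abstract lists these outcomes as secondary. Guideline adherence, the primary outcome, is analysed by logistic regression.

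**The concern.** A proportion of children scanned cannot exceed 1, and its sampling variance is smaller than its mean. Children also move between activities in groups, and programming differs by day. Each service visit therefore has its own deviation, which a service-level intercept cannot absorb. Poisson regression represents neither feature unless something is added to it.

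The model family is a stated choice and sits beside outcome definitions that it does not match. That makes it more than a detail left for later. Research questions 2 and 3, the effectiveness half of the hybrid design, rest on this sentence. Their confidence intervals could be too wide or much too narrow, depending on how the sentence is implemented.

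**Working it through.** The plan gives no error rate or power for these outcomes. Its 75 services per arm refers to the primary binary outcome, so there is no figure to reproduce here.

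**Inputs.** From the article: 96 services per arm, three assessments, alpha 0.05. Assumed: 30% of child-scans active, 30 to 1000 child-scans per visit, and the service-level and visit-level SDs. As a plausibility check, take 10 children (the eligibility minimum), an illustrative six scans per hour, and sessions of about 2 h and 3.5 h. That gives 10 × 6 × 5.5 = 330 child-scans per visit.

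**Reading 1: the proportion is the response.** With a log link, multiplying the response by 100 leaves the log ratio unchanged but divides the Poisson standard error by √100 = 10. Take a mean proportion of 0.3 in 96 services. Each arm-by-visit total is then 28.8 on the 0-1 scale and 2880 on the 0-100 scale. With the service effect conditioned out, the standard error of the group-by-time contrast is √(4/28.8) = 0.373 or √(4/2880) = 0.037. The data are the same, but the test statistic differs tenfold. Simulation under no effect (300 child-scans, visit SD 0, 0.2 and 0.5 on the logit scale) gave these rejection rates:
- 0-1 scale: 0.0%, 0.0%, 0.0%
- 0-100 scale: 0.0%, 2.2%, 29.6%

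**Reading 2: counts with an offset, service intercept only, model-based standard errors.** Let N be child-scans per visit, p the active share, μ = Np, and s the visit-level SD on the log scale. The true variance of a visit's log count is about (1−p)/μ + s². The Poisson model takes it to be 1/μ. The ratio of true to assumed variance is

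R = (1−p) + μs², and the type I error is 2Φ(−1.96/√R).

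With p = 0.3 and N = 300, μ = 90:

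| s | R | Type I error, formula | Type I error, simulation |
|---|---|---|---|
| 0 | 0.70 | 2% | 2% |
| 0.1 | 0.70 + 0.90 = 1.60 | 12% | 12% |
| 0.2 | 0.70 + 3.60 = 4.30 | 35% | 37% |
| 0.3 | 0.70 + 8.10 = 8.80 | 51% | 55% |

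The simulation used 96 services per arm, one baseline and one follow-up visit, service SD 0.3 and 2000 runs per cell. With N = 100 (μ = 30), the formula gives 5%, 16% and 29% for s = 0.1, 0.2 and 0.3; the simulation gave 5%, 18% and 32%.

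**Check with three visits.** A second simulation used all three assessments, service SD 0.5, visit SD on the logit scale and 1000 runs per cell. At p = 0.3, a logit SD corresponds to about 0.7 times that SD on the log scale.

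| Child-scans per visit | Visit SD 0 | Visit SD 0.2 | Visit SD 0.5 |
|---|---|---|---|
| 30 | 1.5% | 3.8% | 12.9% |
| 100 | 1.3% | 7.2% | 34.7% |
| 300 | 1.8% | 18.6% | 56.2% |
| 1000 | 2.0% | 42.8% | 77.5% |

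A full random-intercept Poisson fit by adaptive quadrature (200 runs) at 300 child-scans gave 1.0%, 19.5% and 49.5%. At 100 child-scans and SD 0.5 it gave 35.5%.

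**After a fix.** Across all count-with-offset scenarios, the same Poisson model with service-clustered robust standard errors rejected 4.4% to 7.0% of the time. A linear comparison of change in service-level proportions rejected 4.4% to 6.8% of the time.

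**The case against.** The strongest defence is that a condensed article names a model family and leaves its specification to the full analysis plan. Poisson with a log-denominator offset and robust standard errors is a recognised way to estimate a ratio of proportions. Nothing in the article rules it out, and it held the error rate near 5% above. This stands, and it limits how far the point can go. Several stronger readings are tempting but lack support:

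- **The plan fits only a service effect.** The random-effects structure is not given. Reading 2 is a plausible default, not a stated one.
- **Poisson is simply the wrong model.** With an offset and clustered errors it is valid. The mismatch lies in the bare model with its own standard errors.
- **The analysis would test attendance rather than activity.** The outcomes are defined as proportions and the denominator is recorded. There is no reason to suppose it would be dropped.
- **Averaging two observers invalidates the counts, including staff behaviour categories.** Averaging is stated only for reliability-scan timestamps. It can produce half-counts, but robust estimation accommodates them, so discarding the second observer's data is not warranted. For staff, the text says that reliability is captured and analysed in the same way; it does not say that behaviour categories are averaged.
- **Type I error will be inflated.** Without visit-level variation, or with a 0-1 response, the test is conservative.

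What survives is that the article does state a model, that model does not match the article's own outcome definitions, and neither plain reading gives dependable standard errors.

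**Conclusion.** The point holds in limited form. The named model does not match bounded proportion outcomes, and without further specification its standard errors are unreliable in both directions. With pooled counts and a service intercept only, the type I error is about 2% without visit-level variation and about 12% to 55% for visit SD 0.1 to 0.3 on the log scale at 300 child-scans per visit. The scan numbers, the 30% active share, the SDs and the service-only structure are all assumptions. The range illustrates how sensitive the test is and does not predict this trial's error rate. The scale dependence in Reading 1 needs no assumption about variability. Because the outcomes are secondary and the primary logistic analysis is untouched, this should be corrected before analysis but is not a must-fix.

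**What to change.** State the response and its denominator for each outcome: children active or on screens out of children scanned, and enabling behaviour out of staff scans. Then name one of these:

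- a binomial mixed model for the service-by-visit proportion, with a service random intercept and a service-by-visit random effect;
- a linear mixed model on the session proportion;
- Poisson regression with offset log(number scanned) and service-clustered robust standard errors, if a ratio is wanted. This version also copes with half-counts from averaged reliability scans.

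The cost is a change of wording, with no new data. Where visits vary, the intervals will be wider than those the bare model would report.

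Suggested text, if Poisson is kept: *The number of children (or staff) in the target category per service visit will be modelled by Poisson regression with the log of the number scanned as offset and standard errors clustered by service.*

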**Methods:**

192 OSHC services across Australia will be recruited. 96 services will be randomly allocated to receive the Activated OSHC program. OSHC coordinators will complete online surveys examining physical activity and screen time scheduling, cost, acceptability, and feasibility. Primary outcome; changes in the proportion of intervention and control services meeting OSHC sector physical activity and screen time guidelines, and secondary outcomes; changes in children’s physical activity and screen time behaviours; changes in staff behaviour will be assessed using mixed-effects regression models.

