### Participants and recruitment

Eligible OSHC services will be those that offer both before- and after-school care, for at least 10 children on a typical day, have internet access, and have an OSHC coordinator who is able to speak, read, and write in English. A list of eligible OSHC services within 120 km radii of Adelaide (in the state of South Australia), Newcastle (New South Wales), and Perth (Western Australia), will be obtained from the Australian Children’s Education and Care Quality Authority (ACECQA) and will serve as the sampling frame. To enhance the sample’s representativeness, services will be divided into socioeconomic status (SES) tertiles, based on their ‘Index of Community Socio-Educational Advantage’ (ICSEA) score. ICSEA is an Australian government metric that provides a standardised measure of the socio-educational backgrounds of students, taking into account various factors such as parents’ education levels, occupation, and location (urban/rural) among others.^17^ Metropolitan services will be invited in a randomly selected order (computer generated sequence), and with a recruitment goal of 54 services per state (18 low, 18 medium, and 18 high SES) totalling 162 metropolitan services (Fig. 2). OSHC coordinators will be emailed a study information package, followed by telephone contact to confirm eligibility. For logistical reasons, services within a 0-50 km radius will be approached first. If the quota is not met, we will extend recruitment to services within 50–75 km, 75–100 km, and then 100–120 km radii until we reach our target. We will also recruit 30 regional services across the three states using convenience sampling. Regional services will be invited within geographic clusters (so that data collection is feasible) until 10 services in each state (total = 30) are recruited.

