### Allocation and blinding

Following baseline data collection, OSHC services will be randomised by research staff in a 1:1 allocation ratio to either the intervention or control group. Randomisation will be stratified based on state and location (metropolitan or regional), with metropolitan services further stratified by SES tertile. Randomization will be undertaken using REDCap software. Block randomisation (3 states x 4 groups, i.e. regional or one of three metropolitan SES tertiles) will be used to ensure group allocation is equal.

Services randomised to the intervention group will receive access to the Activated OSHC program and will be encouraged to become an Accredited Activated OSHC service. Services randomised to the control group will be encouraged to continue with their usual programming and will receive access to the Activated OSHC program following completion of the 12-month assessment.

Participants cannot be blinded to condition, however, research staff conducting the assessment visits will be blinded to group allocation.

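### The models' stated stratification factors are not those used to randomise: location is left out and the 30 regional services have no level of their own

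*Protocol article*

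**What the plan says.** Three sections of the protocol article bear on this.

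- **Allocation and blinding** sets the design: "Randomisation will be stratified based on state and location (metropolitan or regional), with metropolitan services further stratified by SES tertile". It then gives the block structure as "3 states x 4 groups, i.e. regional or one of three metropolitan SES tertiles". Regional is one undivided group within each state, and SES tertile subdivides the metropolitan services only.
- **Participants and recruitment** follows the same structure. The metropolitan goal is "54 services per state (18 low, 18 medium, and 18 high SES) totalling 162 metropolitan services". Regional services are a convenience sample, invited "until 10 services in each state (total = 30) are recruited", with no SES quota. That section also says that "services will be divided into socioeconomic status (SES) tertiles, based on their ‘Index of Community Socio-Educational Advantage’ (ICSEA) score".
- **Sample size and statistical analysis** specifies the models: "The models will be adjusted by the stratification factors: state and socioeconomic status tertile". The same paragraph commits to intention to treat. No other section adds location to the models.

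**The concern.** The analysis sentence presents state and SES tertile as the complete list of factors stratified on. Set against the allocation section, it is wrong in two respects: location is missing, and SES tertile was not a stratification factor for regional services.

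An analyst working from the text has to choose between two codings. One assigns each regional service an ICSEA tertile that played no part in its allocation and pools it with metropolitan services of that tertile. The other takes the tertile from the randomisation strata, where regional services have none, so the covariate is undefined for them and a complete-case fit loses them. The two codings give different covariate sets and possibly different analysis sets for the primary outcome. A prespecified primary model should not leave that open.

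**Working it through.** **1. Strata in the design.** From Allocation and blinding: 3 states × (3 metropolitan SES tertiles + 1 regional group) = 12 strata, of which 9 are metropolitan and 3 regional. This reproduces the article's own 3 × 4 structure.

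**2. Services in those strata.** From Participants and recruitment: 3 × 3 × 18 = 162 metropolitan and 3 × 10 = 30 regional. The total is 192, which matches the abstract: "192 OSHC services across Australia will be recruited. 96 services will be randomly allocated to receive the Activated OSHC program". Per arm this is 81 + 15 = 96.

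**3. Cells the model can represent.** State (3) × SES tertile (3) = 9 cells, none of them regional. The services whose randomisation stratum has no counterpart in the model number 30/192 = 15.6%.

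**4. Parameters.** As written: state 2 df + tertile 2 df = 4 df. Matched to the randomisation: state 2 df + four-level group 3 df = 5 df. The difference is 1 df.

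**5. Consequence if regional services are kept with a tertile.** Allocation is 1:1 within strata, so leaving out location does not confound the comparison. It can make standard errors somewhat conservative, and in a logistic model it changes the covariates that the odds ratio is conditional on. The size was checked by simulation under these assumptions: one time point, logistic model, 162 metropolitan and 30 regional services in 12 strata, metropolitan control rate 41%, the odds ratio implied by 41% versus 61%, random tertiles for regional services, 3,000 runs per setting. The documents give no regional rate, so a range was used.

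| Assumed regional control rate | Power, as written | Power, four-level group |
|---|---|---|
| 21% | 78.8% | 79.1% |
| 31% | 79.1% | 79.1% |
| 41% | 80.1% | 79.9% |
| 61% | 79.1% | 79.3% |

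Type I error was 4.3% versus 4.7% at a regional rate of 21%, and 4.4% versus 4.6% at 61%. Every difference is below half a percentage point.

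**6. Consequence if regional services are dropped (worst case).** The standard error is multiplied by √(192/162) = 1.089, about 9%. The number per arm falls from 96 to 81, against the 75 that the article says it needs.

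Power for a single time point, two-sided, unpooled and without covariates is Φ(0.20/SE − 1.96), with SE = √[(0.41×0.59 + 0.61×0.39)/n]. This gives 0.808 at n = 96 and 0.738 at n = 81. These figures do not describe the planned analysis, which uses three repeated measures. The article states no within-service correlation. If the three measures are averaged and the correlation is assumed to be 0.66, the value at which 97 × (1 + 2 × 0.66)/3 ≈ 75, power is about 81% at 75 per arm, 84% at 81 and 90% at 96.

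**The case against.** The strongest reply is that little turns on this. The sentence in Participants and recruitment that divides services into ICSEA tertiles is not limited to metropolitan services; only the quotas are. Regional services may therefore have a tertile and the model may be fittable for all 192. Nothing in the article says they would be deleted, and it states intention to treat and allows for multiple imputation. In a condensed article, SES tertile may also be shorthand for the four-level group, with the exact coding left to the analysis plan.

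Most of this stands, and it limits the consequence. A reader might infer that 30 services will be lost and that power will fall from 81% to 74%. The documents do not support that: deletion is one possible reading that they do not state, and those power figures are a single-time-point worst case. Even then, the 81 metropolitan services per arm exceed the stated 75, because the regional services were recruited on top of that requirement. A reader might also infer that the treatment comparison is biased or that power is materially lost when the services are kept; the simulation shows neither.

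The reply does not remove the mismatch. The article names the stratification factors explicitly, and the names disagree with its own allocation section. If shorthand was meant, the text does not say so. That is a contradiction within the document and not a detail deferred to another one.

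**Conclusion.** The point holds as a misstatement of the stratification factors, of minor severity. It affects how 30 of 192 services (15.6%) enter the logistic and Poisson models.

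- **Kept with a tertile:** no bias expected. Any conservatism in the standard errors is likely small: under half a percentage point of power in the settings tried. This rests on assumed regional rates of 21% to 61% and a single-time-point logistic model; the Poisson models were not simulated.
- **Covariate undefined, services dropped:** a departure from intention to treat, with a standard error about 9% larger and 81 per arm remaining before attrition. This is a worst case that the documents do not state.

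The reason to act is that the primary model should use the groups the trial randomises by, and the coding choice should be closed before analysis. No sample-size figure changes.

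**What to change.** Replace the adjustment sentence in Sample size and statistical analysis with:

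> Models will be adjusted for the randomisation strata: state (3 levels) and location/SES group (4 levels: regional, metropolitan low, metropolitan medium, metropolitan high).

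Apply it to both the mixed-effects logistic model and the mixed-effects Poisson models. If an ICSEA tertile for regional services is wanted as well, describe it as an additional covariate and not as a stratification factor.

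The cost is one sentence and one extra parameter per model. No new data are needed, because the four-level group is already required to randomise each service. Every randomised service then has a defined covariate value.
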